The St. George Respiratory questionnaire and the UCSD shortness of breath questionnaire capture data on the most common symptoms of lung cancer. The questionnaires address the frequency and severity of symptoms, along with how these symptoms affect everyday activities. These questionnaires will be completed by all study subjects every six months.

The EQ-5D (Euro-Qol – 5 dimension) is a standardized, validated, internally consistent quality of life questionnaire specifically designed for measuring health related quality of life. It provides a simple descriptive profile and a single preference-based index for global health status. The EQ-5D was originally designed to complement other instruments such as the SF-36 or disease-specific questionnaires but is now increasingly used as a 'stand alone' measure. The EQ-5D has recently been weighted according to the social preferences of the US population by Shaw et al (2005). The corresponding set of EQ-5D health state preferences will be used to derive the global health related quality of life for our study. There are in excess of 800 published references to the EQ-5D and this measure will be used more frequently for US studies now that the US population preference norms are available. This questionnaire will be completed by all study subjects every six months.

The Paper Standard Gamble questionnaire17 will be used to collect patients’ utility outcome (effectiveness) of the cost-effectiveness analysis. With Standard Gamble, we are asking how much risk the patient is willing to take for a chance of perfect health. Because it involves uncertainty, while EQ-5D does not, Standard Gamble is the only true utility measure. Originally, a facilitator used props during a face-to-face encounter with the patient. This method is expensive because it requires the facilitator’s time. For ease-of-administration reasons, the paper-base tool (Paper Standard Gamble) was designed and good results have been achieved.18 This form will be administered by trained research personnel at baseline and yearly thereafter for the subset of study subjects who are CCHS patients.

Table 1: Study Forms

| **Study Form** | **Screening** | **Baseline** | **Every 6 Months**  +/- 2 weeks | **Annual**  **Visits**  +/- 1month | **Malignant Nodule**  Additional follow-up  Every 2 Months |
| --- | --- | --- | --- | --- | --- |
| Screening Form | X |  |  |  |  |
| Eligibility Form |  | X |  |  |  |
| Medical Release Form |  | X | X | X | X  (Obtain as needed) |
| Baseline Visit Form |  | X |  |  |  |
| Follow-up / Medical Utilization Form |  |  | X | X | X |
| Radiology Reading Form  (with and with out CAD) |  | X |  | X |  |
| Nodule Form |  | X | X | X | X |
| Shortness of Breath Questionnaire (UCSD) |  | X | X | X |  |
| St. George’s Respiratory Questionnaire |  | X | X | X |  |
| EQ-5D Questionnaire |  | X | X | X |  |
| Paper Standard Gamble Questionnaire* |  | X |  | X |  |

*Administered to CC patients only; the cost effectiveness analysis will be performed only on subjects who are CC patients at the time of study enrollment.

11.2 **MISSING AND DELINQUENT DATA**

The study trained research personnel will review incoming paper forms for clarity and completeness of the relevant information. If there are questions or missing data the study trained research personnel will telephone the patient for clarification.

11.3 **DATABASE**

The CC’s department of Quantitative Health Sciences will serve as the Data Coordinating Center (DCC) for this study. Data management will be hybrid in nature, in that data will be transmitted to the DCC from a variety of sources, to reside in a central database. In addition, a small amount of data will originate at the DCC, i.e. randomization information.

The basic data management principles include: 1. The DCC will hold the central database. All data originate from validated data systems, transferred to the CC DCC. All electronic data capture or upload processes will be completely tested and validated, but represent a small part of the entire process, in that, data dictionaries and variable definitions are predefined by the originating source.

There are four data sources for this study: 1. The demographics, EQ-5D and paper standard gamble, symptoms report, and medical resource utilization forms, completed by study subjects; 2. radiology report forms completed by individual radiologists; 3. randomization information maintained by the DCC; and 4. Medicare DRG and CPT information (costs related). With the exception of the randomization information, all data originate outside of the DCC. Data are entered through a validated web-enabled user interface, and electronically captured and stored at the DCC

A web-enabled application utilizing system and user based permissions will allow the clinical sites to enroll, randomize, and collect study related information within the DCC centralized database. The application will utilize data field validation when appropriate to ensure data entry/capture accuracy of key variables. The central data repository is an Oracle database stored on state-of-the-art servers with the DCC’s physically secure data center. The DCC utilizes industry best practices to ensure data quality, data security and data backup.

At regular intervals, data will be queried by the DCC using Oracle Discoverer and Oracle Reports to perform consistency checks on key variables and between forms. As required, data will be extracted from the master Oracle database to SAS datasets for statistical analysis. Each dataset will contain a data dictionary, a complete description of how the data was extracted and version identification as well as key dates and timing sequences.

11.4 **RANDOMIZATION PROGRAM**

A restricted randomization will be conducted centrally by the Cleveland Clinic (CC), Data Collection Center(CC/0 in a manner designed 1) to limit the probability of substantial imbalance in the allocation of subjects to study arms within a site, and 2) to limit the probability of substantial imbalances between study arms in the prognostic stratification variables.

Randomization will be implemented using a secure web-enabled system residing at the CC. A unique subject identification number and site location will be assigned to each subject. Randomization will be implemented by informing the enrolling site, of the subject assignment to screening or placebo screening. A subject will be considered to have been randomized to the assigned study arm and included in the intent-to-treat population once the subject identification number has been assigned.

12.0 **END POINT ASSESSMENT**

12.1 **PRIMARY ENDPOINT ASSESSMENT**

The primary outcome measure is the frequency of advanced-stage cancers detected during the course of the 2 ½ year study. These advanced-stage cancers may be detected during the study's planned screenings, through progression of preclinical disease to clinical symptomatic disease, and, less frequently, during medical testing/screening for other purposes (e.g. presurgical work-up). Advanced-stage cancers will be defined as stage III or IV cancers and will be assessed as clinically indicated, which usually includes PET imaging, additional invasive testing (i.e. tissue sampling), and sometimes brain imaging.

12.2 **SECONDARY ENDPOINT ASSESSMENT**

A secondary endpoint is the presence/absence of symptomatic lung cancer. To assess this outcome, an expert outcome review committee, consisting of a pulmonologist and an oncologist, will be convened at the end of the study (after March 2011). The committee members, each working independently, will review all cases of diagnosed, pathology-proven lung cancer as well as all deaths. Committee members will be blinded to the randomization assignment of the subjects and results of screening tests. Based on the subject’s self-reported symptoms assessment during the study and their medical records, and death certificates (if appropriate and available) the committee members will determine whether the subject is asymptomatic or has symptoms that correlate with their diagnosis of lung cancer. Subjects determined to have symptoms of lung cancer by both committee members will be classified as events for calculation of this secondary endpoint. In cases where the two committee members disagree, the committee members will meet to discuss the cases and reach consensus. Deaths due to lung cancer and deaths due to the management or treatment of diagnosed lung cancer will also be classified as events. For all events, committee members will decide on, to within 6 months, the time at which the subject developed symptoms.

Note that for the assessment of the primary and secondary endpoints, subjects who are determined to have lung cancer that has metastasized will be considered a censored event at the time of diagnosis. These subjects’ lung cancer will not be classified as events in the assessment of the primary and secondary endpoints.

Definition of "Advanced Symptomatic Disease":

The following criteria will be assessed by the Outcomes Review. All three criteria must hold.

1. The patient has been diagnosed with non-small cell carcinoma, stage II or

higher, or small cell carcinoma, any stage.

2. The patient has experienced a symptom that led them to seek contact with a

physician since the time of the last study visit; or at the time of their next study

visit, the patient has developed a new symptom or a change in a chronic

symptom within the past 6 weeks, that did not yet lead to a doctor's visit.

3. The symptom(s) described in #2 are felt to be related to the diagnosis of lung

cancer as adjudicated by the Outcomes Review Committee.

For the other secondary endpoints, the committee will review the medical records and self-reported symptoms assessment of all deaths and determine if the death is due to lung cancer.

13.0 **STATISTICAL ANALYSIS PLAN**

13.1 **PRIMARY AIMS:**

Analyses will be based on an intent-to-treat perspective. We will test the null hypothesis that at the time of diagnosis the frequency of advanced-stage cancers is the same for screened and unscreened groups; the alternative hypothesis is that the frequency of advanced-stage cancers is different for screened and unscreened groups. These hypotheses will be tested at the end of the two and a half-year study, i.e. after March 31, 2011. The frequency of advanced-stage cancers in the two study arms will be compared using logistic regression analysis. A model will be fit to describe the probability of advanced-stage cancer as a function of the following independent variables: age, gender, symptoms status at the time of enrollment into the study (i.e. symptoms present or not present), study arm, and two-way interactions with study arm. The fit of the model will be assessed using the Hosmer-Lemeshaw goodness of fit test. The coefficients for study arm and interactions with study arm will be assessed, after adjusting for other covariates, using a likelihood ratio test with significance level of 0.05 (two-tailed).

13.2 **SECONDARY AIMS:**

One of the secondary aims of the study is to determine whether lung cancer screening using chest x-rays and CAD reduces the incidence of symptomatic advanced lung cancer relative to no screening. The observed cumulative incidence of symptomatic advanced lung cancer, measured in events per person per years observed, will be compared between the two study arms. The analysis will be carried out from an intent-to-treat perspective.

The incidence rate of symptomatic lung cancer will be estimated as follows

Incidence rate at time *t*= [# events by *t*] / [# of person-years at risk until *t*].

where “event” is the development of symptoms due to lung cancer or death due to treatment for the disease or lung cancer death (whichever is observed first). These events will be determined by the outcome review committee at the end of the study (after March 2011). The number of person-years at risk is equal to t – e, where t is the smaller of [time at which the subject experienced symptoms of lung cancer, time at which the subject was lost to follow-up if the subject did not die from lung cancer or from its treatment before *t*, time at which the subject died from lung cancer or its treatment, *t*], and

e is the number of study months before the subject was enrolled into the study (i.e. e=0 at the start of the study).

The following null hypothesis will be tested: the incidence rates of the screened and control subjects are equal. The alternative hypothesis is the incidence rates of the screened and control subjects are not equal. A stratified analysis will be used. There will be four strata:

- age < 65 years at enrollment; none/mild pulmonary symptoms at enrollment
- age > 65 years at enrollment; none/mild pulmonary symptoms at enrollment
- age < 65 years at enrollment; moderate pulmonary symptoms at enrollment
- age > 65 years at enrollment; moderate pulmonary symptoms at enrollment.

Note that only four strata were chosen because the overall number of events will be small. These particular four strata were chosen because we expect that age and pulmonary health at enrollment are the strongest predictors of the development of lung cancer and curability of lung cancer.

For each stratum i, the data can be summarized as follows:

Screened Control Total

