Chest x-rays will be interpreted by chest-radiologists. The radiologist will first read the case without CAD, and then with CAD. The findings will be reported by the radiologist on the Radiology Reading Form (case report form), which includes reader findings and recommendations for follow-up. If the radiologist does not find an actionable nodule and does not recommend follow-up for the subject, then the images will be read by a second chest radiologist. This second reading will be blinded to the first interpretation. The findings will be reported by the second radiologist on Radiology Reader Form (case report form). Subjects who underwent a chest x-ray and were found to have an actionable finding on the chest x-ray by one of the radiologists will be mailed a Findings Report form, along with the dictated medical record reports, via certified mail. The Findings Report form will include all actionable findings found by the radiologist. Chest x-rays will be interpreted and reported within approximately four to six weeks of the chest x-ray, and subjects with actionable findings will be notified shortly thereafter.

Subjects with actionable findings will be phoned after written notification to answer any questions the subject has, and to encourage a follow-up visit with a primary care physician or pulmonologist. The recommendations of the radiologist will not be mandated to the subject’s physician; rather, subjects and their physicians together will determine the plan for follow-up testing and treatment, as appropriate.

Subjects with no primary care physician will be offered a list of physicians who could receive the results of their positive screening and oversee the management of follow-up recommended as a result of screening. Under-insured participants will be offered information about local sources of financial assistance and health care services. We will limit the number of subjects that are uninsured at baseline to 10% to ensure that the study objectives are not compromised by an inadequate number of subjects who pursue recommended follow-up.

9.0 **ANNUAL SCREENINGS**

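### The primary endpoint (stage III/IV) rests on clinical staging with no blinded review, although a blinded committee already reviews every pathology-proven lung cancer for secondary endpoints

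*Protocol*

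**What the plan says.** **Primary endpoint (Protocol 12.1).** Advanced-stage cancers "will be defined as stage III or IV cancers and will be assessed as clinically indicated". The assessment is one "which usually includes PET imaging, additional invasive testing (i.e. tissue sampling), and sometimes brain imaging", so it is not a fixed set of tests. Section 8.0 leaves the follow-up plan to the subject and the subject's own physician. Section 10.0 has research personnel collect staging information by telephone or mail.

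**Committee (Protocol 12.2).** The section opens with the secondary endpoint of symptomatic lung cancer and continues: "To assess this outcome, an expert outcome review committee" is convened at the end of the study. Its two members work independently and "will review all cases of diagnosed, pathology-proven lung cancer as well as all deaths". On masking: "Committee members will be blinded to the randomization assignment of the subjects and results of screening tests". For advanced symptomatic disease: "The following criteria will be assessed by the Outcomes Review. All three criteria must hold". Criterion 1 opens "The patient has been diagnosed with non-small cell carcinoma, stage II or" higher, and small cell carcinoma qualifies at any stage. The committee also rules on whether deaths are due to lung cancer. Nothing assigns it the stage III/IV decision.

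**Who may know the arm.** Section 6.0 blinds subjects and research personnel. Under section 8.0, a screened subject with an actionable finding "will be mailed a Findings Report form, along with the dictated medical record reports, via certified mail". The subject is then phoned and encouraged to see a physician.

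**The concern.** The stronger safeguard protects a secondary endpoint, while the primary endpoint depends on whatever stage was recorded in routine care. A placebo subject has no image, so a Findings Report shows that the subject was in the screening arm. A physician who stages a screen-detected cancer may therefore know the arm. If that knowledge affects how borderline disease is labelled, the difference enters the primary comparison and cannot be told apart from a screening effect. Few events are expected, so a small number of stage calls could decide the test.

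This is not a detail left to a later document. Section 12.1 itself states how the primary outcome is assessed, and a better-protected method already exists in the next section.

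**Working it through.** **1. Reproduce the planned counts (section 14.0, N = 4,000 per arm).** Stated inputs: prevalence 1%, annual incidence 0.5%, annual loss 10%, compliance 90%, sensitivity 85%, risk reduction 70%, and 30% and 15% advanced at the baseline and incident screens. Symptoms are uniform over 30 months, giving 12/30 = 0.4 at 12 months and 24/30 = 0.8 at 24 months. N' = 4,000 × 0.99 = 3,960.

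*Placebo*
- Year one: 0.9 × 0.01 × 0.4 × 4,000 = 14.40
- Year two, prevalent disease: 0.81 × 0.01 × 0.8 × 4,000 = 25.92
- Incident disease: 0.9 × 0.005 × 0.4 × 3,960 = 7.13
- Total 47.4 (Table 2: 47.5)

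*Screened*
- Advanced when detected: M = 10.20 at baseline, M' = 2.04 at the incident screen
- Detected, then progressed: 3.66 (year one), 6.59 (year two), 1.47 (after the incident screen)
- Undetected, then progressed: 2.15, 3.88, 0.96
- Total 31.0 (Table 2: 30.9)

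Both counts agree with Table 2 to within 0.1.

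**2. Planned contrast.** 47.5 − 30.9 = 16.6 cancers.

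The year-two terms for prevalent disease use the cumulative 24-month rate and are added to the year-one terms, so year-one cases appear to be counted twice. Using only the further 12 months (0.8 − 0.4 = 0.4) for those terms:
- Placebo: 14.40 + 12.96 + 7.13 = 34.5
- Screened: 10.20 + 2.04 + 3.66 + 3.30 + 1.47 + 2.15 + 1.94 + 0.96 = 25.7
- Contrast: 34.5 − 25.7 = 8.8

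**3. Share of screened-arm events where the physician may know the arm.** Screen-detected: 10.20 + 2.04 + 3.66 + 6.59 + 1.47 = 23.96 of 31.0, or 77%. Without the double count: 10.20 + 2.04 + 3.66 + 3.30 + 1.47 = 20.67 of 25.7, or 80%. These are planning-model figures. They show where knowledge of the arm is possible, not that staging was biased.

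**4. Effect of reclassifying 2 to 3 cases in one arm (assumed; not in the documents).**
- On 16.6: 2/16.6 = 12%, 3/16.6 = 18%
- On 8.8: 2/8.8 = 23%, 3/8.8 = 34%

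**5. Sensitivity of the test near the planned counts** (unadjusted chi-square, no continuity correction, 4,000 per arm; a stand-in for the planned logistic model):

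| Placebo | Screened | p |
|---|---|---|
| 47 | 29 | 0.038 |
| 47 | 30 | 0.052 |
| 47 | 31 | 0.069 |

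One stage call can move the result across 0.05.

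**6. Illustration with no true effect** (47.5 expected in each arm). Suppose a share of screened-arm stage III/IV cancers were recorded at a lower stage. The shares are assumptions. The chance of a significant result favouring screening would rise from 2.5% to 4.3% (5% share), 7.3% (10%), 17.7% (20%) or 35.7% (30%). Over-recording would push the other way.

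**The case against.** Reserving the committee for symptoms is defensible. Whether a symptom is due to lung cancer is a judgement, whereas stage rests largely on imaging and tissue and is less open to observer bias. Review procedures and the staging edition are often left to a charter or SAP. This keeps the point an improvement rather than an error, and the absence of a named edition is not itself a fault. It does not explain why a blinded review of the same cases should stop short of the primary endpoint.

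A reader might infer more than the documents support, in four ways:

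- **That the committee already makes a stage judgement which is then ignored.** The committee must use stage for non-small cell disease, but criterion 1 speaks of what the patient has been diagnosed with, which fits accepting the recorded stage. Its cut is stage II or higher, and small cell needs no stage. It never has to judge the II/III border, so the III/IV call would be new work.
- **That staging is unblinded throughout.** Knowledge of the arm is an inference, supported only for screen-detected cases, where the report goes to the subject and the physician may receive it. Nothing shows it for placebo, screen-negative or interval cases. Section 11.4 says the enrolling site is informed of the assignment, which conflicts with section 6.0 and should be reconciled, but it concerns sites and not treating physicians.
- **That the bias favours screening.** More intensive work-up of screen-detected cancers could raise their recorded stage and count against screening; under-calling would do the reverse.
- **That blinded review cures the problem.** A review after March 2011 cannot supply tests that were never done, and medical records may reveal how a nodule was found.

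**Conclusion.** The point holds as a cheap improvement. Section 12.1 bases the primary endpoint on clinical staging with no blinded reviewer, while section 12.2 already sends every pathology-proven lung cancer and every death to a blinded committee for secondary purposes.

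The exposure matters because the contrast is small: 16.6 cancers as planned, about 8.8 without the apparent double count. A shift of 2 to 3 cases in one arm would be 12-18% or 23-34% of it. The size of that shift is assumed and its direction unknown; the documents give no evidence that misclassification would occur. The conclusion also rests on the inference that physicians of screen-detected cases may learn the arm. Differences in work-up intensity would remain whoever calls the stage.

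**What to change.** - **Reconcile first.** The section 12.2 note says lung cancers that have metastasized are censored and are not events for the primary or secondary endpoints. Section 12.1 counts stage IV. The two must be brought into line before a committee stage is used for the primary analysis.
- **Add the stage call to the existing review.** Have the Outcomes Review Committee record stage I/II versus III/IV for each pathology-proven lung cancer, under one named staging edition, at the same blinded review and with screening results masked in the records.
- **Use it.** Make committee stage the basis of the primary endpoint, and report clinician-recorded stage as a sensitivity analysis, so that the effect of stage calling is visible.
- **State the remaining limitation.** Blinded review addresses how stage is called from the available evidence, not differences between arms in how thoroughly subjects were worked up.

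**Cost.** No new staff and no new tests. The committee reviews these cases anyway; section 14.0 implies 8,000 × 1% = 80 prevalent cancers and 8,000 × 0.5% = 40 new ones a year, before losses and undiagnosed disease. Reviews become somewhat longer, since a III/IV call is an added judgement, and records must be masked, which may be imperfect for screen-detected cases. The planned sample size does not change.

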The role of CAD as applied to chest x-rays is to minimize the potential errors by the interpreter and to identify potential cancerous lesions that can be missed. By improving the accuracy and consistency of radiological diagnosis, CAD will assist the radiologist in detecting early disease that can be potentially missed, allowing for early intervention and management16. We propose to use one of these systems in a screening setting. This will be the first controlled trial of chest x-ray screening in which there is a placebo control group, and the first chest x-ray screening trial that uses CAD to improve our ability to detect subtle cancers.

3.0 **OBJECTIVES**

3.1 **PRIMARY OBJECTIVE**

The primary aim of the study is to report and compare the frequency of advanced-stage lung cancers at the end of the 2 ½ year study between screened and placebo groups.

3.2 **SECONDARY OBJECTIVES**

The secondary aims are as follows:

- Determine whether lung cancer screening with chest x-rays and computer aided detection (CAD) reduces the incidence of symptomatic advanced lung cancer compared to no screening in a high-risk population. The presence of advanced symptomatic lung cancer will be determined by the Outcomes Review Committee.
- Compare the disease-specific mortality between screening with chest x-ray and CAD versus no screening. This is the endpoint used in many RCTs of lung cancer screening; thus, we will be able to compare our study results to the results of these other trials.
- Compare the all-cause mortality rate between screening with chest x-ray and CAD versus no screening. This endpoint includes all deaths including those attributed directly and indirectly to screening.
- Compare the length of time between randomization and the incidence of symptomatic advanced lung cancer for screened subjects versus controls. This analysis will provide data about how screening might delay the development of advanced lung cancer.
- Measure the monetary cost relative to the quality of life between screening with chest x-ray and CAD versus no screening. The comparison of quality of life since randomization between the two study arms will reveal differences over time due to screening. Coupled with an assessment of monetary costs, cost-utility of screening will be measured. Note that the cost-utility analysis will be performed on a subset of the study participants.

4.0 **SELECTION OF PATIENTS**

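### The note in Section 12.2 that censors metastasised lung cancer contradicts the stage III or IV primary endpoint in Section 12.1, and it must be reconciled before endpoint review

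*Protocol*

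**What the plan says.** Section 12.1 defines the primary outcome: "Advanced-stage cancers will be defined as stage III or IV cancers". Section 12.2 then adds a note that names both the primary and the secondary endpoints. Under it, "subjects who are determined to have lung cancer that has metastasized will be considered a censored event at the time of diagnosis", and these subjects' cancers "will not be classified as events in the assessment of the primary and secondary endpoints". The note makes no exception for stage IV and does not define metastasised.

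Other places set event rules with no such exclusion:

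- Section 12.2, symptomatic endpoint: "Deaths due to lung cancer and deaths due to the management or treatment of diagnosed lung cancer will also be classified as events".
- Section 12.2, definition of advanced symptomatic disease, first criterion: "The patient has been diagnosed with non-small cell carcinoma, stage II or" higher, or small cell carcinoma of any stage.
- Section 13.2, incidence rate: an event "is the development of symptoms due to lung cancer or death due to treatment for the disease or lung cancer death", whichever comes first.
- Section 3.2 lists disease-specific and all-cause mortality as secondary comparisons, again without exception.
- Section 13.1 analyses the primary endpoint by logistic regression on an intent-to-treat basis.
- Section 14 builds Table 2 from formulas that take off nothing for metastatic disease.

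**The concern.** By ordinary staging convention, distant metastasis is what places a lung cancer in stage IV. Section 12.1 therefore counts a class of cancers that the note in 12.2 takes out. Two analysts, each following a different sentence, would report different primary results.

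The loss may not fall equally on the arms. The Abstract's rationale is that screening finds disease at an earlier stage. Under the note, a cancer that presents as stage IV without screening is not an event, while the same cancer found at stage III through screening is one. The rule could thus remove more events from the placebo arm than from the screened arm and shrink a real difference.

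The note also cannot be carried out as written in the primary analysis. Logistic regression has no censoring, and the protocol does not say whether such a subject becomes a non-event or is dropped. Dropping randomised subjects would sit badly with the intent-to-treat statement.

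**Working it through.** **1. The note against the other rules**

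| Place | Rule | Fits the note? |
|---|---|---|
| 12.1 | Stage III or IV is a primary event | No: stage IV is removed |
| 12.2, deaths | Lung cancer deaths are events in the symptomatic endpoint | Unclear for deaths after a metastatic diagnosis |
| 12.2, advanced symptomatic disease | Non-small cell stage II or higher; small cell any stage | No: both include metastatic disease |
| 13.1 | Logistic regression | No: no censoring |
| 13.2 | Time at risk ends at symptoms, loss, lung cancer or treatment death, or the analysis time | No: no term for a metastatic diagnosis |
| 14 | Event formulas | No: nothing deducted |

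**2. Reproducing Table 2 at N = 4,000 per arm**

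Inputs from Section 14: prevalence 0.01, annual incidence 0.005, annual loss 0.10, compliance 0.90, sensitivity 0.85, risk reduction 0.70. Symptoms develop uniformly over 30 months, so the rates are 12/30 = 0.40 and 24/30 = 0.80. N' = 4,000 − 40 = 3,960.

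Placebo:
- 0.9 × 0.01 × 0.40 × 4,000 = 14.40
- 0.81 × 0.01 × 0.80 × 4,000 = 25.92
- 0.9 × 0.005 × 0.40 × 3,960 = 7.13
- Sum 47.45 (stated 47.5)

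Screened: M = 0.01 × 0.85 × 0.30 × 4,000 = 10.20 and M' = 0.9 × 0.9 × 0.005 × 0.85 × 0.15 × 3,960 = 2.04. The eight terms of Section 14 are 10.20 + 3.66 + 2.15 + 2.04 + 6.59 + 3.88 + 1.47 + 0.96. They sum to 30.97 from unrounded terms (stated 30.9).

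The total is 78.4, as stated. The table reproduces with no deduction for metastatic disease, so the sample size assumes that the note does not apply.

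**3. Baseline power**

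Section 14 gives 1.19% against 0.77%, 4,000 per arm, two-sided 5%. With mean rate p = 0.0098:

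z = [|p1 − p2|√n − 1.96√(2p(1 − p))] / √(p1(1 − p1) + p2(1 − p2)) = (0.0042 × 63.25 − 1.96 × 0.1393) / 0.1393 = −0.05

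Power is therefore 47.9%, not the stated 77%. With 8,000 per arm the same formula gives 76.9%. That discrepancy is a separate error; 48% is the like-for-like baseline here.

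**4. Applying the note with an equal metastatic share f in both arms**

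The protocol does not give f, so the values are assumptions. Events are 78.4 × (1 − f). Both design rates are multiplied by (1 − f) and put through the formula in step 3.

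| f | Events (placebo, screened) | Total | Rates | Power |
|---|---|---|---|---|
| 0 | 47.5, 30.9 | 78.4 | 1.19% vs 0.77% | 47.9% |
| 20% | 38.0, 24.7 | 62.7 | 0.952% vs 0.616% | 39.9% |
| 40% | 28.5, 18.5 | 47.0 | 0.714% vs 0.462% | 31.3% |
| 50% | 23.8, 15.5 | 39.2 | 0.595% vs 0.385% | 26.9% |
| 60% | 19.0, 12.4 | 31.4 | 0.476% vs 0.308% | 22.4% |

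Section 14 requires at least 70 events for its model. The total drops below 70 once f exceeds 1 − 70/78.4 = 10.7%.

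**5. Applying the note with unequal shares**

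The event ratio without the note is 30.9/47.5 = 0.65. With assumed shares of 60% (placebo) and 40% (screened), events are 47.5 × 0.40 = 19.0 and 30.9 × 0.60 = 18.5. The ratio is 18.54/19.0 = 0.98.

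**The case against.** The best defence is that the note is a stray sentence. It may have been meant for tumours that spread to the lung from another primary, and every other event rule points to counting stage IV cancers, so a sensible analyst would ignore it. The likely intent deserves weight, and this is better called an internal contradiction than a deliberate design choice. But the note describes lung cancer that has metastasised and refers to these subjects' lung cancer, which is not how one describes a secondary tumour. It also names the primary endpoint expressly. It states a rule that conflicts with the endpoint definition, so it is not a detail left to an analysis plan.

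Three stronger readings are tempting, and the documents do not support them.

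- A reader might infer that most lung cancer deaths would be censored. The protocol gives no share of deaths that follow a metastatic diagnosis. Section 12.2 itself counts lung cancer deaths as events, and the note speaks of the subjects' lung cancer, not of their deaths. Whether such deaths are removed is ambiguous.
- A reader might set the 22% to 40% power beside the stated 77% and blame the note for the whole gap. Against the recomputed 48%, the loss is about 8 to 26 percentage points.
- A reader might infer that screening would look harmful. In the 60% against 40% illustration the ratio approaches 1 but does not pass it. With 40% in the screened arm, reversal needs a placebo share above 1 − 0.60 × 30.9/47.5 = 61%, and nothing in the protocol establishes such a gap.

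**Conclusion.** The contradiction is certain: it follows from the wording of Sections 12.1 and 12.2 alone. Because it concerns what counts as a primary event, it must be fixed.

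The size of the effect is conditional on the note being applied literally, on metastasised meaning distant spread, on removed cases staying in the denominator as non-events, and on Table 2 being taken as given. With an equal share of 20% to 60%, 16 to 47 of the 78.4 expected events are lost. The shortfall against the protocol's own 70-event minimum hardly depends on the share chosen, since about 11% is enough. If metastasised were taken to include nodal spread, some stage III cancers would go as well.

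Unequal shares would bias the comparison towards no difference; the 0.98 is an illustration of that mechanism, not an estimate. The effect on disease-specific mortality remains an ambiguity to be resolved.

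**What to change.** Reconcile the passages before the outcome review committee begins its work (after March 2011), because a choice made once outcomes are known would be post hoc.

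- Delete the two-sentence note in Section 12.2. If tumours spread to the lung from elsewhere were meant, replace it with: 'Cancers metastatic to the lung from a non-lung primary are not lung cancer events.'
- State that stage IV primary lung cancer counts as a primary event.
- State that the existing rule counting lung cancer deaths applies whether or not the cancer had metastasised.

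With these changes the event definitions in Sections 12 and 13 agree on metastatic disease, and the Table 2 counts need no deduction for it. The stated power still needs its own correction. The cost is a few sentences of text, with no change to visits, data collection or subject burden.
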